## Abstract

**ABSTRACT:**

**Introduction:**

The night-time economy comprises various sectors, including hospitality, transportation and entertainment, which generate substantial revenues and contribute to employment opportunities. Furthermore, the night-time economy provides spaces for leisure activities, cultural expression and social interaction. On-trade alcohol premises (places where consumers can buy and consume alcohol such as bars, pubs, clubs and restaurants) are a significant component of this night-time economy, functioning as focal points for socialising, entertainment and cultural events. However, when on-trade alcohol premises stay open later at night, this can be associated with negative public health impacts including increased alcohol consumption, intoxication, assaults, injuries and burden on public services including ambulance call outs, hospitalisations and increased impacts on criminal justice services. The evidence on the societal impact of policies to ‘later’ trading hours for bars and clubs in the night-time economy is limited. This protocol details the design of an economic evaluation of policy to later trading hours for bars and clubs in the night-time economy alongside the ELEPHANT study (National Institute for Health and Care Research (NIHR) Public Health Research, ref:129885).

**Methods and analysis:**

The research design is an economic evaluation alongside a natural experiment within the ELEPHANT study carried out in Glasgow and Aberdeen. The economic evaluation has been designed to identify, measure and value prospective resource impacts and outcomes to assess the costs and consequences of local policy changes regarding late night trading hours for bars and clubs. A number of economic evaluation frameworks will be employed. A cost-effectiveness analysis (CEA) is appropriate for assessing the effectiveness of complex interventions when the impacts of policy are measured in natural units. Therefore, a CEA will be conducted for the primary consequence, alcohol-related ambulance call-outs, using a health service sector perspective. Since this outcome is essentially a cost, the CEA will also be reported as a cost-analysis. A cost-consequence analysis will also be performed for the primary and secondary consequences including all ambulance call-outs and reported crimes to evaluate the full economic impacts of later trading hours for bars and clubs in the night-time economy. The analysis will be conducted from a wider societal perspective, including health sector, criminal justice system, business and third sector perspectives and will be in line with the recent National Institute for Health and Care Excellence guidance and recommendations.

**Ethics and dissemination:**

The economic evaluation of the ELEPHANT study will be conducted using secondary data. Thus, no ethical approval is required for this economic evaluation. However, ethical approval for the ELEPHANT study has been granted from the University of Stirling’s General Research Ethics Committee, and prior consent has also been obtained from the participants, if involved. The results of this study will be disseminated through peer-reviewed publications in journals and national and international conferences.

STRENGTHS AND LIMITATIONS OF THIS STUDYThis is the first economic evaluation of a natural experiment to evaluate the impact of later trading hours for bars and clubs on alcohol-related ambulance call-outs and reported crimes in Scotland.A broad societal perspective, including health services, criminal justice system, business and a third sector perspective will be considered.This study will include a cost-effectiveness analysis, a cost-analysis and a cost-consequence analysis framework.This natural experiment nature of this study means that we cannot collect and incorporate all economic data such as benefits/gains to the night-time economy, alcohol-related road traffic accidents and productivity losses to individuals.

## Introduction

The night-time economy (NTE) refers to the economic activity that takes place during the evening and early morning hours between 18.00 and 6.00.^1^,^3^ The NTE comprises various sectors, including transportation, entertainment and hospitality, which generate substantial revenues and contribute to employment opportunities.^3 4^ The NTE provides spaces for leisure activities, cultural expression and social interaction. In 2019, 1.95 million people were employed in the NTE, which produced 5% of the overall gross domestic product (GDP) of the UK between 2011 and 2019.^5^ On-trade alcohol premises (places where consumers can buy and consume alcohol such as bars, pubs, clubs and restaurants) are a significant component of the NTE, functioning as focal points for socialising, entertainment and cultural events.^1^ Hence, in addition to contributing to revenue generation beyond the traditional 9-to-5 workday, alcohol consumption in the NTE is a popular pastime for many individuals and a growing aspect of night-time activities in urban environments.^2 4^ However, the proliferation of later trading hours for bars and clubs in the NTE can lead to excessive alcohol consumption and also raises concerns related to public health, safety and potential negative impacts including late night ambulance call-outs and increased crimes and assaults.^2^,^46^

Alcohol consumption is a major contributor to the burden of both communicable and non-communicable diseases globally,^12^,^15^ is the leading cause of preventable death in people aged 15–49 years, underpins increased crime, road traffic accidents and violence^13^,^16^ and imposes a huge health and economic burden.^12^,^17^ In 2016, harmful use of alcohol led to the premature deaths of three million people globally, accounting for 5.3% of all deaths, including 0.9 million injury-related deaths attributable to road injuries, self-harm and interpersonal violence.^12^ Furthermore, it is responsible for 132.6 million disability-adjusted life years (DALYs) annually, which accounts for 5.1% of the total global burden of disease and injury.^12^ An international systematic review and modelling study estimated the economic costs of harmful alcohol consumption to be an average of 2.6% of GDP in 2019.^18^ In England, alcohol-specific deaths were 7556 in 2021 and there were 342 795 alcohol-specific hospital admissions between 2021 and 2022.^19^ In 2004, 9.5% of presentations in the emergency department in Australia and New Zealand were found to be alcohol-associated.^20^ Between 2006 and 2014, the rate of alcohol-related emergency department visits in the USA increased from 1223 to 1802 per 100 000 people, resulting in a 272% increase in total costs from US$4.1 billion to US$15.3 billion.^21^ In Scotland, 1276 people died in 2022 from a cause wholly attributable to alcohol (alcohol-specific) with a 2% increase from 1245 in 2021; that is, an average of 25 people every week.^22^ In 2022/2023, 31 206 alcohol-related hospital admissions were recorded in Scotland; among them, 28 800 were admitted in general acute hospitals, which is equivalent to 532 hospital stays per 100 000 population and is about 3.4 times greater than the number of alcohol-related hospital stays recorded in 1981/1982.^23 24^

The harmful use of alcohol incurred an estimated cost of £3.56 billion (2007) for the Scottish economy, which is equivalent to £6.2 billion (inflation adjusted) in 2024; this translates to around £1756 per adult (adult: aged between 16 years and 65 years based on 2022 census data).^25^ Of this £3.56 billion (2007), health and social care expenses were estimated to account for £500 million (ie, inflation adjusted £869 million in 2024) a year.^25^ There is substantial evidence that reducing alcohol availability, regulating selling hours, increasing the price of alcohol and regulating marketing policy can prevent alcohol-related harms.^26^,^29^ In contrast, late-night alcohol sales are associated with increased rates of crimes, injuries, disorder and use of emergency services including accident and emergency (A&E) services, criminal justice system services, ambulance services and fire services. In the northeast of England from April 2009 to March 2010, 10% of ambulance call-outs were alcohol-related through a manual check of electronic records of northeast ambulance service, with a peak concentration between midnight and 1.00, largely on Friday and Saturday nights.^30^ Using a novel free-text algorithm, 16% of ambulance call-outs were found to be associated with alcohol-related incidents in Scotland.^31^ However, alcohol-related ambulance call-outs increased to 18.5% on weekends and further to 28.0% on weekend nights (from 18.00 to 6.00).^31^ In addition, they incurred an estimated £31.5 million costs in 2019 based on the average cost of an ambulance call-out.^31 32^ In 2019/2020, in Scotland, 44% of violent crimes involved offenders who were under the influence of alcohol; further, 20% of victims reported drinking alcohol immediately prior to the incidents.^33^ The annual cost of assaults in Scotland is estimated at >£1.5 billion despite progress made in tackling violence.^34^

On weekends in Scotland in 2019, the highest concentration of alcohol-related ambulance call-outs occurred between 21.00 and 1.00, whereas the highest concentration of non-alcohol-related call-outs appeared between 10.00 and 21.00; revealing that alcohol-related ambulance call-outs are more prevalent after midnight.^31^ Systematic reviews show that extensions in late night opening of alcohol premises are associated with increased intoxication, assaults, injuries and burden on public services.^7^,^11^ An extra 1-hour extension to opening times of alcohol outlets in 18 Norwegian cities was associated with a 16% increase in violent crimes from 22.00 to 5.00^35^ and similarly was associated with 34% more alcohol-related ambulance call-outs from 2.00 to 6.00 in Amsterdam, Netherlands.^36^ Opening hours changed from 22.00 to 23.00 in Scotland in the ‘70s, and women were found (in a before/after survey) to have slightly increased consumption and a slight shift in drinking at later times.^37^

Economic evaluation is a useful tool for informing decision making and public sector resource allocation.^38^ Previous systematic reviews of economic evaluation of alcohol prevention policies show that reducing/restricting alcohol selling hours and days reduced alcohol consumption and is likely to be cost-effective in preventing DALYs.^39^,^41^ However, a review article on the methodological challenges of economic evaluation for alcohol prevention policies identified major methodological limitations in the available literature including lack of consideration of multisectoral and long-term outcomes, lack of wider societal perspective and limited use of recommended economic evaluation methods, for example, cost-consequence analysis (CCA) and cost-benefit analysis.^42^ Restricted retail hours and days are estimated to have contributed to the avoidance of 1009 DALYs in Estonia,^43^ 2163 DALYs in Denmark^44^ and 2700 DALYs in Australia.^45^ These studies, however, also reported limitations including quality of data, lack of evidence of intervention effects and being restricted to a health sector perspective.^43^,^45^ Hence, this study aims to conduct an economic evaluation from a wider societal perspective, with a more robust method to estimate policy effect.

No previous study in the UK has considered the impact of later trading hours for bars and clubs on alcohol-related ambulance call-outs, and there have been no studies in Scotland since the ‘70s.^37^ Moreover, no studies have evaluated the economic impact of later trading hours for bars and clubs in Scotland from the viewpoint of the health service or taken a wider societal perspective which considers impacts on the judicial sector and retail. Economic evaluations using natural experiment methodology based on routine data are becoming increasingly popular.^46^,^48^ Although randomised controlled trials (RCTs) have been recognised as the ‘gold standard’ for assessing causal effects, natural experiments (in which the effects of a naturally occurring event or phenomenon are being observed) are identified as a practical solution for evaluating policies where randomisation is often not possible and sometimes unethical.^40 49^ However, there is still a dearth of literature reporting economic evaluations alongside natural experiments. In addition, the existing literature on economic evaluation alongside RCTs does not focus on important methodological aspects for conducting economic evaluations alongside natural experiments, particularly those related to study design.^48^ For example, it provides limited guidance on addressing biases and confounding effects raised from a lack of randomisation, selecting appropriate comparators and managing routine data from multiple sources. In proposing an economic evaluation of two policy changes alongside a natural experiment in Aberdeen and Glasgow cities, this protocol addresses an important gap in the literature.

### Objective

The aim of this economic evaluation alongside a natural experiment is to evaluate the economic impact of two policy changes in Aberdeen and Glasgow. Economic evaluation includes a cost-effectiveness analysis (CEA) for the primary outcome (alcohol-related ambulance call-outs) from a healthcare perspective and a cost analysis transforming the primary outcome into a cost (alcohol-related ambulance call-outs) from a healthcare perspective. A CCA is also reported for the primary and secondary outcomes (all ambulance call-outs and reported crimes) from a broader societal perspective. Outcomes will be reported in terms of ‘consequences’, in line with a CCA framework recommended by the National Institute for Health and Care Excellence for reporting public health economic evaluations.^50^

## Methods and analysis

### The policy changes: later trading hours for bars and clubs in Glasgow and Aberdeen

In Glasgow, as of 12 April 2019, under a scheme planned by the Glasgow Licensing Board (GLB), 10 nightclubs among the 17 applications submitted (among 1350 on-premises outlets) were permitted to implement a variation in their licence, enabling them to open for an extra hour until 4.00 for at least 12 months. The scheme was described by the Licensing Board as an ‘opportunity to reward and continue to encourage great practice in the nightclub trade’, as the extra hour was only granted to premises meeting certain criteria. The licence holder had to demonstrate, to the satisfaction of the GLB, not only that the premises made a positive contribution to the late-night economy, but that they invested in safety and security measures for both staff and customers and promoted the licensing objectives. The scheme was subsequently expanded before and after the COVID-19 pandemic when all nightclubs/bars were closed by public health measures.

In Aberdeen, the local licensing board changed their policy to remove a requirement for late-night venues to provide ‘significant entertainment’, following a period when the term had been very broadly interpreted. The changes took place from 2017 such that, initially, premises that provided ‘significant entertainment’, and later any premises, were allowed to request/apply to stay open later as a result of changes in the new statement of licensing policy. From November 2018, bars and pubs (which previously had to close at various times up to 1.00) applied to expand their hours, some to 2.00 and some to 3.00, and these extensions were granted. Existing nightclubs in Aberdeen had already been permitted to open to 3.00. To date, approximately 38 bars/pubs (among 430 on-premises outlets) have been granted the later trading hours, bringing them closer to or up to the same closing time as nightclubs. Although both policy changes involve later trading hours for bars and clubs, the scope and level of exposure in Aberdeen, measured by the number of premises and the hours permitted, is greater than in Glasgow.

### Setting and location

In this natural experiment, the selection of target population and study location is constrained by the location of policy changes/implementation.^48^ This study includes two Scottish cities as intervention sites (*the estimated effect will be at city level*), where 10 licensed alcohol premises in Glasgow and 38 licensed alcohol premises in Aberdeen were permitted to operate with later trading hours. So, our study target population will be those residents in these cities. The outcomes in these intervention cities will be compared with concurrent control areas to assess the impact of later trading hours. Control areas will be selected from other Scottish cities where such policies are not in place. Additionally, we will generate a synthetic control for both Aberdeen and Glasgow. The control selection procedure and synthetic control methodology are described below. To develop a controlled before-and-after evaluation, we will consider the dates from which the later closing time was permitted to be used by premises.

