**Figure 2 F2:**
[figure not shown]
Flow diagram for the control selection procedure.

In this study, we will assess the appropriateness of the 30 Scottish councils/cities (except intervention cities—Aberdeen and Glasgow) as potential controls. No policy changes that were comparable to those in Aberdeen and Glasgow took place during our initial assessment. Later trading hours were temporarily changed for holidays (eg, Christmas and New Year), but we expect that intervention cities were similarly impacted. The appropriateness of the potential control candidates will be tested by visually and statistically assessing the assumption of parallel trends.^59^ Graphically, we will observe the preintervention differences between the intervention and control groups. If the parallel test assumption holds, then the preintervention differences will be constant over time. There are no formal statistical tests for this assumption, and passing the parallel test does not necessarily mean that the parallel trend is true.^59^ However, failing the parallel tests will make the parallel trends assumption less plausible.

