If none of the potential control candidates satisfy the parallel trends assumption, we will proceed with an uncontrolled ITS study design (figure 2). In addition, we will construct a synthetic control based on all potential control candidates since synthetic control does not need to satisfy parallel trends and will proceed with a controlled ITS study design.^60^ The synthetic control method (SCM) is widely recommended for ITS designs where multiple prospective control groups are available.^52 61^ The SCM is a data-driven process that builds a control series by calculating a weighted average of potential controls.^61^ To generate weights for the SCM, we will collect data from all Scottish councils/cities in addition to Glasgow and Aberdeen. The weights will be generated based on pre-intervention outcomes of potential control groups so that the preintervention trend of synthetic control matches well with the intervention. This process will be followed twice to generate synthetic controls for Aberdeen and Glasgow. Along with preintervention outcomes, other covariates representing time-varying confounding such as per capita gross disposable household income,^62^ number of alcohol premises/population-adjusted alcohol premises^63^ and weather (mean temperature and rainfall from the Centre for Environmental Data Analysis archive) will be used to generate weights for the synthetic control. In order to determine more accurate weights for the synthetic control series, we will incorporate population size-adjusted alcohol-related ambulance call-out and reported crimes rates for all regions in Scotland. We anticipate that, by using population-adjusted rates, the SCM series will yield a closer match to the observed outcomes prior to the intervention.

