#### Perspectives

The base-case analysis (CEA) will be conducted from an National Health Service (NHS) perspective.^58^ We will identify, measure and value the cost of ambulance services, emergency services and hospitalisation services to inform decision makers with a particular focus on the health sector (table 1). The later trading hours may not only impact health services, but may increase criminal justice system costs.^35 36^ Hence, in line with the array of health and non-health sectors consequences, the CCA will incorporate health services, the criminal justice system and societal perspectives. In addition, in the sensitivity analysis, retailers’ and third sector organisations’ perspectives will be incorporated into the societal perspective.

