### Economic data analysis

#### Analysis of costs and consequences

The economic evaluation will be conducted separately for Glasgow and Aberdeen. First, we will evaluate the impact of policy changes on harms, then we will conduct a CEA, cost analysis and CCA. Regression methods will be used to estimate effectiveness, that is, the impact of policy changes in Aberdeen and Glasgow. We will fit autoregressive integrated moving average (ARIMA) models with the weekly total counts for the primary and secondary consequences to assess the impact of policy changes (table 1). Such models account for autocorrelation and underlying temporal trends, and we will use Akaike information criterion and Bayesian information criterion to determine the best fitting ARIMA models. After a best fitting model is determined, we will then add the intervention variables to measure the effect size (impact of policy changes).

We will assess whether changes in the primary outcome (alcohol-related ambulance call-outs) have been caused by later trading hours. Where fewer or greater numbers of alcohol-related ambulance call-outs are found to have resulted from the policy changes, the unit cost of each resource will be multiplied by the absolute number of fewer or additional outcomes/consequences, for each city, before and after the policy changes.

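### Events are counted and costed within the city but reported from NHS, criminal justice and societal perspectives, so any harm moved across council boundaries would misstate those costs

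*Protocol article*

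**What the plan says.** Under Setting and location, the protocol article states that "the estimated effect will be at city level". It adds: "So, our study target population will be those residents in these cities".

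Under Analysis of costs and consequences, it fixes the costing rule: "the unit cost of each resource will be multiplied by the absolute number of fewer or additional outcomes/consequences, for each city".

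Under Perspectives, it says whose costs these are: "The base-case analysis (CEA) will be conducted from an National Health Service (NHS) perspective", and "the CCA will incorporate health services, the criminal justice system and societal perspectives". The Overview of the economic analysis adds that the cost-consequence analysis is meant to cover every cost and consequence that can feasibly be measured.

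Under Comparators, the other councils have one role. As candidate controls, "we will assess the appropriateness of the 30 Scottish councils/cities"; for synthetic-control weights, "we will collect data from all Scottish councils/cities in addition to Glasgow and Aberdeen". With a control, the city-minus-control difference becomes the outcome series.

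Displacement, spillover and movement across council boundaries are not mentioned in the Comparators section, in the scenarios under Uncertainty and sensitivity analysis, or in the limitations under Reporting and discussion.

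**The concern.** The area over which events are counted is narrower than the bodies whose costs are reported. The outcome data come from the Scottish Ambulance Service and Police Scotland, and the health unit costs from Scottish Health Service data. None of these bodies stops at the city boundary.

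Suppose some people who would have gone out in a bordering council go to the city instead because venues close later. A call-out that moves with them raises the city count and is priced in full. The matching fall next door is never credited, although the ambulance service and the NHS carry no additional event. In the other direction, people who leave the city later may come to harm in a bordering council on the way home. That event is additional to the NHS and the justice system, and the city count misses it.

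This differs from choosing an uncontaminated control. Even with a control that the policy does not touch, the city estimate remains a city total. What is at stake is whether a reader of the NHS or societal cost can tell additional harm from relocated harm. The article says that results will inform licensing decisions and go to public health bodies beyond the two cities.

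**Working it through.** The article gives no displacement share, effect size or unit cost, so there is no stated figure to reproduce. What follows is an accounting identity on assumed inputs.

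**Inputs**
- E: true increase in events inside the city. Set to 100 for illustration.
- d: share of E relocated from other councils. Not in the documents; assumed 0, 10% and 25%.
- s: extra events in bordering councils caused by the policy, as a share of E. Not in the documents; assumed 10% and 25%.
- w: weight of an affected bordering council in the control series. No exclusion of bordering councils is stated, so w could lie between 0 and 1.

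**Step 1. Relocation into the city, unaffected control.** Events charged = E. Net events to the NHS or society = E(1-d). Ratio of charged to net = 1/(1-d).
- d = 0: 100/100 = 1.00
- d = 10%: 100/90 = 1.11
- d = 25%: 100/75 = 1.33

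With a constant unit cost, the same ratios apply to cost.

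**Step 2. Spill outward, unaffected control.** Events charged = E. Net events = E(1+s). Ratio = 1/(1+s).
- s = 10%: 100/110 = 0.91
- s = 25%: 100/125 = 0.80

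If both occur, net events = E(1-d+s), and the sign of the error depends on which is larger.

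**Step 3. A bordering council used as control.** The difference series then contains the neighbour's fall as well. On an equal population scale (assumed), the estimate is E(1+wd) and its ratio to the net change is (1+wd)/(1-d). With w = 1:
- d = 10%: 110/90 = 1.22
- d = 25%: 125/75 = 1.67

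So a control does not net displacement off; one drawn from a donor council enlarges the error.

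**Step 4. What the location field means.** The Consequences section lists council name among the ambulance data fields without saying whether it is the place of the incident or of residence. Steps 1 to 3 assume place of incident. If it is residence, a visitor's call-out in the city is counted in the home council, and the city series means something different. The article names residents as its target population while analysing area counts, so the point needs stating.

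**The case against.** The strongest reply is that the plan never claims a national cost. A perspective names the sectors whose costs count; it does not draw a map. The geographic scope is local in the Objective, Setting and location, Study design and the costing rule, and for a licensing board the city figure is the relevant one. This stands to the extent that a cost plainly labelled as city-level is not an error. It does not remove the difficulty that the article labels the result NHS and societal without that qualification.

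A reader might infer that relocated call-outs and crimes are in fact being charged as new cost, and that the NHS cost is therefore overstated. The documents do not support this. They contain no evidence that displacement occurs, and spillover can run outward, so the direction is open. The description of the policy changes also makes a large inflow doubtful. Aberdeen nightclubs could already open until 3.00, so the extended bars did not move the city's latest closing time. In Glasgow, 10 of 1350 on-premises outlets (0.7%) gained an hour at first, although the scheme later grew. Movement between venues within a city is already netted out by city-level estimation.

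The statistical analysis plan is not shown and may treat spillover when choosing controls. That would not settle the point, because this article itself fixes the costing rule and the perspectives. The scenario list is introduced by example, so an added scenario would not contradict it. Finally, a small change in bordering councils could be lost in the noise of whole-council weekly series. That is a fair limit on what the remedy can show.

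**Conclusion.** The mismatch between a city-level count and NHS, criminal justice and societal cost labels is in the text, and changes in neighbouring councils are never counted. The consequence is conditional: if harm crosses council boundaries, the cost under those perspectives is misstated, upward for inflow and downward for outflow. The size is unknown. On assumed shares of 10% and 25%, inflow alone gives overstatement of 1.11 and 1.33, and outflow alone gives 0.91 and 0.80 of the net figure; with neither, the error is nil. These figures rest on an unaffected control, a constant unit cost, and council name meaning place of incident. The planned city-level analysis is not invalid. The point supports a specific, inexpensive addition and a clearer label.

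**What to change.** 1. Keep the city-level estimate as the base case, and label its cost as a city-level cost wherever it appears under an NHS, criminal justice or societal perspective.
2. Add a sensitivity analysis on the council series already being collected. Estimate the change in the councils bordering each city against more distant councils, and report city-only and city-plus-neighbours incremental events and costs side by side, with intervals.
3. In that analysis, do not use bordering councils as controls or as synthetic-control donors.
4. State whether council name in the ambulance data is the place of the incident.

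The cost is extra analysis time; the article plans no new data source that this would require. The net estimate will have a wider interval because more series are summed, and it may be uninformative if the neighbouring change is small. For that reason it should accompany the base case and not replace it.
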